## Abstract

**Background:**

Blood purification plays an important role in the treatment of severe acute pancreatitis. Extracorporeal blood anticoagulation is an important strategy to achieve smooth circulation in blood purification circuits. We aimed to investigate the efficacy, safety, and impact on circulating cytokines of using heparin or nafamostat mesylate anticoagulation in patients with severe acute pancreatitis during continuous renal replacement therapy.

**Methods and analysis:**

This is a single-center randomized controlled study. We plan to recruit adult patients with severe acute pancreatitis from intensive care units for this study. Participants who met the criteria were randomly assigned in a 1:1 ratio, with one group using heparin anticoagulation during continuous renal replacement therapy and the other group using nafamostat mesylate anticoagulation. The primary outcome measure was mean filter life. Secondary outcome measures included changes in Sequential Organ Failure Assessment (SOFA), the Acute Physiology and Chronic Health Evaluation II (APACHE II) score, and inflammatory factors (CRP, PCT, IL-6, IL-8, IL-10, TNF-α) compared with baseline levels on days 1, 3, 5, and 7 after treatment, time to successful initiation of enteral nutrition, blood transfusion requirements, ICU length of stay and total hospitalization days, and follow-up of patients’ blood purification dependency rate and all-cause mortality at 28 days. Safety indicators include the occurrence of any bleeding events (defined by ISTH criteria), filter clotting, and the incidence of heparin-induced thrombocytopenia.

**Discussion:**

The results of this study are expected to provide guidance for the selection of anticoagulant drugs for critically ill patients with severe acute pancreatitis who receive continuous renal replacement Therapy, and to clarify the optimal anticoagulation strategy for this population, thereby optimizing clinical practice for treating SAP patients.

**Clinical trial registration:**

[https://clinicaltrials.gov/], identifier [ChiCTR2500 111161]

## Introduction

### Background and rationale

Severe acute pancreatitis (SAP) is a common type of critical abdominal condition in clinical practice. Due to its rapid progression, SAP frequently prone to cause multiple organ dysfunction or even failure, resulting in high complication and mortality rates (1, 2). In patients with SAP who develop persistent organ failure, the mortality rate can be as high as 40% (3–5). Due to the changes in the body functions and circulation of patients with severe acute pancreatitis, the levels of inflammatory factors in their bodies will show a significant upward trend, thereby triggering a cascading reaction of inflammatory factors and subsequently leading to multiple organ dysfunction (6, 7). Previous studies (1, 6–8) have shown that in the early phase of SAP, the excessive release of inflammatory factors will further aggravate the severity of systemic inflammatory response syndrome and promotes the development of infected pancreatic necrosis. Therefore, inflammatory factors are significant factors influencing the onset and treatment of patients with SAP, and they are also important indicators reflecting the condition of patients with SAP (1, 9, 10).

Blood purification therapy can help restore the immune homeostasis of patients with SAP by removing various inflammatory mediators, inhibiting the cascade of inflammatory reactions, and modulating the immune responses. This approach may prevent the development of various severe complications in SAP patients and improve the clinical outcomes (11–13). Consequently, continuous renal replacement therapy has become one of the important treatment methods for SAP. In continuous renal replacement therapy, effective anticoagulation is essential for ensuring the smooth operation of the filter and achieving the target dialysis dose. Heparin has become a commonly used anticoagulant in clinical practice due to its clear anticoagulant effect and easy monitoring. Moreover, studies have shown that heparin can improve pancreatic microcirculation and mitigate pancreatic tissue damage (14–16). However, heparin may cause bleeding and heparin-induced thrombocytopenia (HIT). Some patients still experience recurrent filter clotting and leading to interruption of continuous renal replacement therapy, even while receiving heparin anticoagulation (17). Furthermore, for patients with clotting disorders or those at risk of bleeding, the use of heparin is usually restricted. Nafamostat mesylate (NM) is a synthetic serine protease inhibitor that can exert anticoagulant effects by directly inhibiting coagulation factors, regulating fibrinolysis, and modulating platelet function (18). In addition, some studies (19–21) have shown that NM can suppress trypsin activity and enhance pancreatic microcirculation, which might be helpful for the treatment of severe acute pancreatitis (SAP). To date, no studies have systematically evaluated or compared the clinical efficacy and safety of nafamostat mesylate versus heparin as anticoagulants in patients with severe acute pancreatitis undergoing continuous renal replacement therapy.

We conducted a randomized controlled trial to compare the efficacy and safety of nafamostat mesylate and heparin as anticoagulants during CRRT in patients with severe acute pancreatitis. The results of this study may provide evidence-based medicine for optimizing anticoagulation strategies in this special population, which will help guide clinical practice and ultimately improve the clinical prognosis of SAP patients.

### Objectives

This study primarily compared the effects of nafamostat mesylate and heparin on the lifespan of blood filters during continuous renal replacement therapy in patients with severe acute pancreatitis. The secondary objective was to evaluate their differential impacts on organ dysfunction, inflammatory and coagulation responses, time to gastrointestinal function recovery, clinical outcomes, and overall safety.

### Trial design

This study was designed as a prospective, single-center, randomized, controlled, open-label clinical trial, and reported in accordance with the SPIRIT 2013 reporting guidelines (22). Participants who meet the criteria will be randomly assigned in a 1:1 ratio to receive either NM or UFH as anticoagulants during the CRRT process. Figure 1 shows the flow chart of the research.

**FIGURE 1 F1:**
[figure not shown]
Flow chart of the research.

## Methods: participants, interventions, and outcomes

### Study setting

This study will be conducted in the Department of Intensive Care Medicine of Weifang People’s Hospital, Weifang, Shandong Province, China. The intensive care unit has a total capacity of 110 beds.

### Eligibility criteria

Participants will be considered for inclusion in the study if they meet the following criteria upon admission to the ICU or during stay in the ICU: (1) adults over 18 years old, (2) diagnosed with severe acute pancreatitis (SAP) according to the revised Atlanta classification (2012), meeting at least one of the following: Persistent organ failure ( > 48 h), or APACHE II score ≥ 8 or SOFA score ≥ 4 at ICU admission, (3) requiring blood purification therapy [continuous renal replacement therapy (CRRT)] due to systemic inflammatory response, acute kidney injury, or hypercytokinemia, (4) informed consent obtained from patient or surrogate.

The exclusion criteria for participants included the following: (1) known hypersensitivity or contraindication to NM or UFH, (2) severe coagulation disorders (INR > 2.0), active major bleeding (such as intracranial hemorrhage, ongoing gastrointestinal bleeding) or recent uncontrolled bleeding and bleeding diseases or platelet count < 30 × 10^9^/L, (3) severe hepatic failure (Child–Pugh C), (4) History of heparin-induced thrombocytopenia (HIT), (5) pregnancy or lactation. (6) Chronic kidney disease requiring dialysis before ICU admission, (7) expected survival < 48 h or refusal to participate.

### Who will obtain informed consent or assent from potential trial participants or authorized surrogates?

Before patients participate in the research, the trained study investigators will explain the objectives, procedures, potential risks and benefits of the study, and answer any questions from each patient or their legal representative in detail. After they fully understand the research and voluntarily agreed to participate, they will sign a written informed consent form. Participation in this study is voluntary. Participants can withdraw from the study at any time without affecting their subsequent treatment.

### Additional consent provisions for collection and use of participant data and biological specimens

Not applicable. The data used in this trial will be obtained from the patients’ medical records generated during hospitalization. The researchers will collect only the information required for this study. To ensure participants’ privacy and data security, all information related to the patients’ identities will be anonymized. This study does not involve the collection, storage or future use of biological samples. Therefore, no supplementary consent form is required for the use of biological samples.

## Interventions

### Explanation for the choice of comparators

Heparin is a commonly used anticoagulant in blood purification therapy, and thus can be used as a suitable control. However, patients with SAP often have a higher risk of bleeding, which limits the use of heparin. Nafamostat mesylate can exert anticoagulant effects by inhibiting coagulation factors, and it metabolizes rapidly, having minimal effects on the entire body. Therefore, the application of nafamostat mesylate is becoming increasingly widespread. Comparing nafamostat with the current practice of heparin will help determine whether it provides safer or more reliable anticoagulation during CRRT in this population.

### Intervention description

The CRRT modality will be standardized as continuous venovenous hemodiafiltration (CVVHDF) throughout the trial. All patients will receive standardized CRRT delivered using the Gambro^®^ Prismaflex system, with a prescribed effluent dose of 20∼35 mL/kg/h. Within this prescribed range, the effluent dose and ultrafiltration rate will be titrated according to the patient’s hemodynamic stability (e.g., mean arterial pressure and vasopressor dose) and the severity of the systemic inflammatory response (e.g., procalcitonin, lactate, and SOFA score), consistent with current practice for CRRT in critically ill patients with hypercytokinemia. Vascular access will be obtained via a double-lumen catheter in the internal jugular or femoral vein.

The participants were randomly assigned to the nafamostat mesylate group or the heparin group. The patients randomly assigned to the NM group will only receive nafamostat mesylate as an anticoagulant during CRRT. Dissolve and prepare the NM injection solution using 5% glucose injection. The prepared nafamostat injection will be continuously injected through the anticoagulant injection tube at the same time as the start of extracorporeal circulation and the initial dose is generally 20–50 mg/h. During treatment, the dose is adjusted dynamically based on comprehensive considerations such as extracorporeal circulation, dialyzer usage, and bleeding risk. The general range of dose adjustment each time is 5–10 mg/h. Patients in the heparin group will only receive standard heparin anticoagulation treatment. At the beginning of treatment, 5–15 U/kg of heparin was injected intravenously for loading therapy. Heparin was then continuously infused through the anticoagulant injection tube at a rate of 5–10 U/kg/h. In case of significant bleeding or clotting events, dosage will be adjusted or anticoagulation discontinued according to protocol.

During the research period, the researchers will not attempt to change or influence other routine clinical treatments for patients with severe acute pancreatitis. The treatment plan will be determined by the clinical staff based on the relevant guidelines for severe acute pancreatitis.

### Criteria for discontinuing or modifying allocated interventions

If the patient experiences any drug-related safety issues (such as severe bleeding, an unexplained decline in hemoglobin, clinically significant coagulation abnormalities, severe hypotension, or an allergic reaction to the study drug), the use of the assigned anticoagulant will be discontinued or adjusted. If appropriate dose adjustments are made but recurrent circuit coagulation still occurs, or if the attending physician determines that the assigned anticoagulant is no longer appropriate for the patient’s condition, further modification of the intervention will be considered. All changes and their corresponding reasons will be documented.

### Strategies to improve adherence to interventions

This intervention will be implemented by trained research staff during the continuous renal replacement therapy (CRRT) process of the patients. The patients are unaware of the intervention measures they are receiving and will not be involved in the medication administration process. The researchers will monitor the patients’ compliance through bedside checklists and daily review of treatment records. Any deviations from the trial protocol will be recorded along with the reasons.

### Relevant concomitant care permitted or prohibited during the trial

The standard treatment measures for severe acute pancreatitis are permitted. As long as they meet the clinical indications, any drugs that do not interfere with continuous renal replacement therapy (CRRT) or designated anticoagulation treatment can be used. Except for the specified protocols, the use of additional systemic anticoagulants is prohibited. Hemoperfusion, combined CRRT–hemoperfusion, or other extracorporeal cytokine adsorption therapies will not be permitted during the intervention period because they may independently alter inflammatory biomarker concentrations and confound assessment of study outcomes. All concomitant treatments and any deviations from the protocol will be recorded.

### Provisions for post-trial care

The potential risks of this study are mainly related to the anticoagulation treatment during continuous renal replacement therapy, which may increase the risk of coagulation abnormalities. After the trial is completed, the participants will continue to receive standard treatment for severe acute pancreatitis. Throughout the entire study period, adverse events will be closely monitored. If any adverse events occur, appropriate medical intervention will be provided promptly.

### Outcomes

The primary endpoint of this study is the average service life of the CRRT circuit or filter. The functional lifespan of CRRT circuit begins when the extracorporeal circulation of blood starts and ends when the circuit is taken out of service by intensive care unit (ICU) staff (when the treatment goal is achieved, death occurs, or the upper limit of 72 h for filters). The reasons for ICU staff to stop the circuit operation included: (1) the transmembrane pressure on both sides of the circuit exceeded 300 mmHg, (2) visible blood clots hindered the blood flow within the machine, (3) the blood pump could not rotate due to blood clot blockage, (4) other (recorded by the bedside staff). The first three reasons are considered to be cases of circuit clotting. If the bedside staff recorded “other” or the reason for stopping the circuit was missing, adjudication is required. Two senior critical care specialists, who were not involved in the research, independently reviewed these cases and adjudicated the reasons for circuit discontinuation. In case of any disagreement, they resolved it through joint consultation. The outcome of the judgment may be one of three types (coagulated, non-coagulated or unknown condition). The circuit that is selectively discontinued due to reasons during the treatment process (such as transfer within the hospital) is regarded as “non-coagulated.”

The secondary endpoints of this study include: 1. SOFA and APACHE II scores were evaluated on days 1, 3, 5, and 7 after enrollment, and the changes from the baseline (ΔSOFA /ΔAPACHE II) were calculated to reflect the trend of disease progression; 2. Serum levels of pancreatic enzymes (amylase and lipase) and PCT, CRP, IL-6, IL-8, IL-10 and TNF-α were measured on days 1, 3, 5, and 7, and their changes from baseline were analyzed; 3. levels of coagulation parameters(include aPTT, PT, fibrinogen, platelet count) were assessed on specific days (day 1, 3, 5, and 7) together with their changes from baseline values; 4. time to successful initiation of enteral nutrition; 5. blood transfusion requirements(RBC, FFP, platelet units), 6. ICU length of stay and total hospitalization days; 7. Clinical outcomes (blood purification dependency rate, length of ventilator use and all-cause mortality at 28 days).

Safety outcomes were defined as the occurrence of any adverse events (AEs), including serious adverse events (SAEs) and adverse drug reactions (ADRs), such as the occurrence of any bleeding events (as defined by the International Society on Thrombosis and Haemostasis), allergic reactions, and heparin-induced thrombocytopenia. Researchers are required to continuously monitor for potential adverse reactions throughout the study. In the event of any adverse event, the researchers will promptly take appropriate measures to ensure the safety of the subjects and keep detailed records. For serious adverse events, researchers are required to report the incidents to the ethics committee within 24 h. Study termination will be considered according to the severity and nature of the event.

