### Assignment of interventions: blinding

#### Who will be blinded

Due to the differences in management methods and monitoring requirements for various intervention measures, it is not feasible to implement blinding for clinical physicians and nurses. Therefore, this trial will be an open-label trial, but the result evaluators and statisticians will not know the specific treatment allocation.

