### Strengths and limitations of this study

This trial has several limitations. First, because it is not feasible to blind bedside clinicians and nurses to the anticoagulant used during CRRT, the trial is open-label, and the primary outcome of filter lifespan is partly determined by bedside staff decisions about when to discontinue the circuit. Even though outcome assessors, adjudicators, and the statistician remain blinded to treatment allocation, awareness of the assigned anticoagulant could subtly influence the threshold at which bedside staff choose to stop a circuit, introducing a theoretical source of bias that blinding of assessment alone cannot fully eliminate. To minimize this risk, we have prespecified objective, mechanically verifiable stopping criteria (transmembrane pressure exceeding 300 mmHg, visible clotting impeding blood flow, or pump failure due to clot obstruction) as the primary safeguard against subjective variation in circuit-discontinuation decisions, and cases in which the recorded reason is missing or classified as “other” are independently adjudicated by two blinded senior intensivists, with disagreements resolved by consensus. Nonetheless, residual detection bias related to the open-label design cannot be entirely excluded and should be considered when interpreting the primary outcome. Second, as a single-center trial, the generalizability of our findings to other institutions and case-mix populations may be limited, and multicenter validation will be needed. Third, resource constraints precluded direct measurement of cytokine clearance across the filter itself, so the anti-inflammatory effect of nafamostat mesylate is inferred from circulating biomarker trends rather than effluent-based clearance data.

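### Blinded adjudication covers only stops recorded as other or missing; no blinded check of the bedside clotting calls is described, and visible clot is not a mechanically verifiable criterion

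*Protocol article*

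**What the plan says.** Outcomes (Protocol article) ends circuit life when ICU staff take the circuit out of service. It lists four reasons for stopping: transmembrane pressure above 300 mmHg; "visible blood clots hindered the blood flow within the machine"; a blood pump that cannot turn because of clot; and other. It then states: "The first three reasons are considered to be cases of circuit clotting".

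Adjudication is triggered only when staff record other "or the reason for stopping the circuit was missing, adjudication is required". Two senior specialists from outside the research "independently reviewed these cases and adjudicated the reasons for circuit discontinuation". The limitations section repeats this scope: such cases "are independently adjudicated by two blinded senior intensivists, with disagreements resolved by consensus".

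Under Who will be blinded, the article says "it is not feasible to implement blinding for clinical physicians and nurses". The limitations section concedes that "awareness of the assigned anticoagulant could subtly influence the threshold at which bedside staff choose to stop a circuit". As its main protection against this it offers the following: "we have prespecified objective, mechanically verifiable stopping criteria". Visible clotting is one of the criteria it lists there.

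**The concern.** The people who choose the stopping moment and assign the clotting reason know the allocation. The blinded step begins only when they have not chosen one of the three clotting reasons. A stop made early because of the drug could be coded as visible clot; it would then count as clotting without reaching the adjudicators.

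Two effects have to be kept apart.

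- **The label.** The clotting call determines the filter-clotting indicator named in the Abstract and the coagulation complications compared under Statistical methods. It also affects the Kaplan–Meier and Cox results if only clotting counts as an event. Statistical methods does not say whether it does.
- **The time.** An early stop shortens the recorded lifespan whatever reason is written down. This acts on the primary endpoint directly, and no review of the reason can restore the lost hours.

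**Working it through.** **Which stops have a blinded check described** (Outcomes, and Strengths and limitations)

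| Recorded reason | Nature of the call | Counted as | Blinded adjudication |
|---|---|---|---|
| Pressure above 300 mmHg | Machine reading | Clotting | No |
| Visible clot hindering flow | Bedside visual judgement | Clotting | No |
| Pump blocked by clot | Machine failure | Clotting | No |
| Other, or missing | Any | Clotted, non-clotted or unknown, as adjudicated | Yes |

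Pressure and pump failure can in principle be confirmed from the machine, although no such comparison is described. Visible clot is the only row that rests on judgement, and it bypasses adjudication.

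**Scale of the primary comparison**

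Inputs from Sample size estimation: SD 8 h, difference 4 h, two-sided alpha 0.05, power 80%.

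1. The plan's own figure: n = 2 × [8 × (1.960 + 0.842) / 4]² = 62.8, so 63 per group; 63 / 0.9 = 70 after 10% dropout. Both stated figures reproduce and are not in dispute.
2. Standard error of the difference with 63 per group: 8 × √(2/63) = 1.425 h.
3. Suppose there is no true difference, but a fraction of circuits in one arm is stopped early. The shift in the mean is fraction × hours. The two-sided rejection rate is Φ(shift/SE − 1.96) + Φ(−shift/SE − 1.96).

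| Assumed fraction | Assumed hours early | Shift | Share of the 4 h target | False-positive rate |
|---|---|---|---|---|
| 10% | 2 h | 0.2 h | 5% | 5.2% |
| 20% | 4 h | 0.8 h | 20% | 8.7% |
| 30% | 4 h | 1.2 h | 30% | 13.4% |

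The fractions and hours are assumptions; the documents give none. The table describes the time effect, which wider adjudication would not reduce. It shows only how sensitive a 4 h comparison is to bedside stopping behaviour.

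**The case against.** The strongest reply is that adjudication is the wrong lever. Lifespan ends at removal whatever the coded reason, so re-reading the reason changes a label and not a time. This stands, and it confines the adjudication gap to the clotting outcome and to any time-to-clotting analysis.

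Other points also stand.

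- A reader might infer that the bedside calls are never verified and that nothing could detect a bias. The documents do not support that. Data management provides audits and source data verification by a team unaware of allocation, and the adherence section provides checklists and daily review of treatment records. These are generic controls, however, and are not said to test whether a clotting call was right.
- A reader might infer that every drug-influenced stop would be coded as visible clot or pump blockage. It could equally be recorded as other and be adjudicated.
- A reader might infer that only the pressure limit is mechanical. A pump that clot prevents from turning is a machine failure, so only visible clot is misdescribed.
- The limitations section says that residual detection bias cannot be excluded. The authors do not claim that their safeguard is complete.

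It can also be argued that a case report form field and a sensitivity analysis belong to the full protocol or the SAP. Their absence is indeed not the finding. The finding rests on what the article does state: which stops are adjudicated, and which criteria it calls mechanically verifiable. Disclosing the bias does not bring visible-clot stops within either safeguard.

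**Conclusion.** The point holds in a limited form. Blinded adjudication is restricted to other or missing reasons, no outcome-specific blinded check of the three clotting calls is described, and the article wrongly groups visible clot with mechanically verifiable criteria. A drug-influenced stop could therefore enter as clotting without blinded review. The exposed results are the filter-clotting outcome and, if non-clotting stops are censored, the Kaplan–Meier and Cox results.

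The further inference that the adjudication gap itself biases mean lifespan is not supported. That bias would come from open-label stopping, which the article discloses and which adjudicating reasons cannot remove.

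The size of any bias is unknown. The range of about 5% to 13% for the false-positive rate depends on assumed shifts of 0.2 to 1.2 h, with the plan's SD of 8 h and 63 per group. At the low end the effect is negligible. This is a worthwhile, inexpensive improvement and not a flaw that invalidates the design.

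**What to change.** The changes concern recording, adjudication and analysis. They do not alter when staff stop a circuit.

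1. Record the machine transmembrane pressure at every stop, and report it by arm and stop reason. This would show whether visible-clot stops occur at different pressures in the two arms.
2. Send stops coded as visible clot without a pressure above 300 mmHg to the same two adjudicators, with the drug name removed.
3. With item 2 in place, add a sensitivity analysis of time to clotting in which only pressure-confirmed, pump-blocked or adjudicated clots are events. State that censoring the remaining stops may be informative. Without item 2 this analysis should not be run, because it would censor unconfirmed visible-clot stops at the very moment the circuits may be clotting.
4. Reword the limitations section so that visible clot is not called mechanically verifiable, and say that adjudication protects the clotting label but not the stopping time.

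The cost is one case report form field, one added analysis, a corrected sentence and some extra time for the two existing adjudicators. Item 1 should be in place prospectively, since a pressure not captured at the stop may be hard to recover.

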### Statistical methods

#### Statistical methods for primary and secondary outcomes

Continuous variables were tested for normality using the Kolmogorov–Smirnov test. Normally distributed data were presented as mean ± standard deviation (SD) and compared using the independent-samples *t*-test. Non-normally distributed variables were reported as median (interquartile range, IQR) and analyzed using the Mann–Whitney U test. Categorical variables were expressed as counts (percentages) and compared using the χ^2^ test or Fisher’s exact test, as appropriate.

In addition, the primary endpoint of this study was the mean lifespan of the hemodialysis filter during CRRT. Kaplan–Meier survival analysis was conducted to compare the cumulative probability of filter life over time, with the log-rank test applied for group comparison. To control for potential confounders (e.g., disease severity scores), multivariable linear regression and Cox proportional hazards models were used as sensitivity analyses.

Secondary outcomes included the changes in disease severity scores (SOFA and APACHE II), pancreatic enzymes (amylase, lipase) and inflammatory biomarkers (PCT, CRP, IL-6, IL-10, TNF-α) measured on Day 1 (baseline), day 3, day 5, and day 7 after randomization. To evaluate time-dependent trends and group differences, a repeated-measures analysis of variance (RM-ANOVA) was applied for normally distributed variables. Baseline disease severity characteristics, including etiology, CTSI/EPIC radiological scores, and the presence and grade of intra-abdominal hypertension, will be summarized descriptively and compared between groups using the χ^2^ test, Fisher’s exact test, or the Mann–Whitney U test, as appropriate. The assumption of sphericity was tested by Mauchly’s test, and when violated, the Greenhouse–Geisser correction was used to adjust degrees of freedom. Differences in change-from-baseline values (ΔSOFA, ΔAPACHE II, and Δbiomarker levels) between groups were analyzed using the independent-samples *t*-test or Mann–Whitney U test, as appropriate. Correlations between the changes in inflammatory markers and changes in severity scores were assessed using Spearman’s rank correlation coefficient.

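### ICU stay, hospital stay and ventilator duration are compared with no rule for death, so if mortality differs between arms, the one with more early deaths can look better

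*Protocol article*

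**What the plan says.** In the protocol article, the Outcomes section lists among the secondary endpoints "ICU length of stay and total hospitalization days", "time to successful initiation of enteral nutrition" and "Clinical outcomes (blood purification dependency rate, length of ventilator use and all-cause mortality at 28 days". Mortality is thus a separate component beside the durations and is not built into them.

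The section on statistical methods for primary and secondary outcomes opens with a general rule by type of variable:

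- Normal continuous data: "Normally distributed data were presented as mean ± standard deviation (SD) and compared using the independent-samples" t-test.
- Other continuous data: "Non-normally distributed variables were reported as median (interquartile range, IQR) and analyzed using the Mann–Whitney U test".
- Categorical data: "Categorical variables were expressed as counts (percentages) and compared using the" chi-square or Fisher's exact test.

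Survival methods appear only in the paragraph on the primary endpoint: "Kaplan–Meier survival analysis was conducted to compare the cumulative probability of filter life over time", with the log-rank test, and Cox regression as a sensitivity analysis. The paragraph on secondary outcomes deals with severity scores, enzymes and biomarkers. It does not name stay, ventilation, enteral nutrition or dependency.

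The section on non-adherence and missing data expects missing data to be rare and names mixed-effects models and multiple imputation. It does not mention death.

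The background section says that in severe acute pancreatitis with persistent organ failure "the mortality rate can be as high as 40" per cent. Persistent organ failure is one of three alternative severity criteria for entry. The only exclusion on prognosis is an expected survival under 48 hours.

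**The concern.** Death ends an ICU stay, a hospital stay and a period of ventilation. Under a plain two-sample test, a patient who dies in the ICU on day 3 contributes a 3-day stay, which ranks as better than the 15-day stay of a patient who recovers. The missing-data rule does not help, because a stay ended by death is fully observed.

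Clinical outcomes are a stated secondary objective, so these comparisons will be interpreted. If one anticoagulant leads to more early deaths, the plan as written can show it shortening stay and ventilation.

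Two related endpoints have a weaker version of the problem. Time to enteral nutrition has no value for a patient who dies or never starts, and imputing one for a patient who died would place feeding after death. The dependency rate has no stated denominator, so how deaths count is open.

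**Working it through.** **The plan's own figure.** The documents give no number for this issue. The only computed figure is the sample size for filter life: 2 × (1.960 + 0.842)² × 8² / 4² = 62.8, so 63 per arm, and 63 / 0.90 = 70. It reproduces, and 70 per arm is used below.

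**Step 1: arithmetic for mean stay.** Assumed, and the same in both arms: survivors stay 20 days, non-survivors 8 days. With mortality *p*, mean stay = (1 − *p*) × 20 + *p* × 8.

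| Mortality | Mean stay |
|---|---|
| 25% | 15.0 + 2.0 = 17.0 days |
| 30% | 14.0 + 2.4 = 16.4 days |
| 40% | 12.0 + 3.2 = 15.2 days |

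The gap between arms is (20 − 8) × the difference in mortality. At 30% vs 40% it is 12 × 0.10 = 1.2 days, and at 25% vs 40% it is 12 × 0.15 = 1.8 days. Both favour the arm with more deaths. At equal mortality the gap is zero.

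**Step 2: simulation of the test.** From the documents: 70 per arm, 28-day follow-up and two-sided 5%, with 40% as the higher mortality in the table. Assumed: underlying ICU stay lognormal with median 14 days and log-scale SD 0.6, identical in both arms; death times truncated exponential within 28 days, with parameter 4, 7 or 14 days (early to later deaths); stay cut at death. There were 1,500 runs per scenario, so the simulation standard error of the percentages below is at most about 1.3 points.

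| Mortality | Median observed stay, early deaths | Median observed stay, later deaths | Mann–Whitney significant in favour of the higher-mortality arm |
|---|---|---|---|
| 40% vs 30% | 8.9 vs 10.4 days | 10.9 vs 11.7 days | about 9–15% of trials |
| 40% vs 20% | 8.9 vs 11.7 days | 10.9 vs 12.5 days | about 23–43% of trials |

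The rate expected in that direction by chance is 2.5%. With equal mortality (30% or 40% in both arms) total rejection was about 4–6%, so the test keeps its size.

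**Step 3: the alternative measure.** On ICU-free days to day 28 with death scored 0, the same simulated patients gave means of about 7.6 vs 8.8 days at 40% vs 30%, and 7.6 vs 10.1 at 40% vs 20%. The direction now agrees with mortality.

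**Step 4: the two other endpoints.**

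- *Time to enteral nutrition* (assumed lognormal, median 4 days, counted only if reached before death). At 40% vs 30% with early deaths the medians were 3.78 vs 3.86 days and rejection was about 5%. The distortion is negligible here.
- *CRRT dependency* (assumed 30% in both arms). If deaths stay in the denominator as not dependent, 0.30 × 0.60 = 18% vs 0.30 × 0.70 = 21%. With survivors as the denominator it is 30% in both arms. Dead or dependent would be 40% + 18% = 58% vs 30% + 21% = 51%.

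**The case against.** The strongest reply is that the article assigns no test to these endpoints by name. The tests reach them through the general opening rule, and the handling of deaths in secondary durations is often left to the analysis plan. This stands in part. However, the general rule covers continuous variables without exception, and survival methods are described only for filter life. The issue is therefore what the stated method does when followed, beyond any missing detail.

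A reader might also infer several stronger things that the documents do not support:

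- **That every one of these endpoints is biased.** The document does not say that deaths count as not dependent. For enteral nutrition, the intention-to-treat and imputation wording does not settle whether non-starters drop out, and the shift is small even if they do.
- **That an early death gives the best possible value.** A patient ventilated for 3 days before dying has more ventilator days than a survivor never ventilated, and late deaths can bring long stays. The direction depends on when deaths occur.
- **That 40% is the expected mortality of the trial.** It is an upper figure for patients with persistent organ failure. Patients can also enter on APACHE II or SOFA alone.
- **That the comparison is biased whatever happens.** It needs a mortality difference between arms, and the documents predict none.

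Finally, 28-day mortality is itself a listed outcome, so a misleading duration would appear beside it. That limits the harm but does not correct the comparison. Free-days are not the only defensible choice either: clearly labelled durations with mortality reported separately can also be interpreted.

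**Conclusion.** The point holds for ICU stay, hospital stay and ventilator duration. The stated tests, with no rule for death, can favour the arm with more early deaths when mortality differs. The size depends on assumptions. It is 1.2 days of mean stay at 30% vs 40% mortality with assumed stays of 20 and 8 days. In the simulation of ICU stay, about 9–15% of trials with 40% vs 30% mortality gave a significant result in the wrong direction, against 2.5% expected. Ventilator duration and hospital stay were not simulated separately, but death truncates them in the same way.

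For time to enteral nutrition the need is a defined analysis set, and the expected distortion is small. For CRRT dependency the bias arises only if deaths count as not dependent, which the document leaves open.

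It does not follow that the trial would hide a harmful drug. These endpoints are secondary, mortality is reported, and the filter-life conclusion and sample size are untouched. The change should be made, but the trial does not hinge on it.

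**What to change.** - **Durations.** Compare ICU-free, hospital-free and ventilator-free days to day 28, with death scored as the worst value. State in advance whether death ties at zero with a survivor who has no free days or ranks below. Show 28-day mortality beside each result, and give raw durations in survivors as description only.
- **Time to enteral nutrition.** Use cumulative incidence with death as a competing event (Gray's test or a Fine–Gray model), censored at day 28, so that patients who die or never start remain in the analysis.
- **CRRT dependency.** Report dead or dependent at day 28, with the two components shown separately.

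**Cost.** This is a change of wording in the protocol and analysis plan, with the ethics approval and registry update that the protocol requires for any modification. Stay, ventilation, start of enteral nutrition and 28-day mortality are already outcomes, so no new measurement should be needed. The downside is less familiar units and measures that combine mortality with duration, which is why the components must be shown. The rule should be fixed before outcome data by arm are seen.
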